## Methods

### Objectives

The aim of the proposed study is twofold. Behavioral analysis of gait and cognitive function together with PET and MRI brain imaging methods will be used to evaluate the molecular basis and neural underpinnings of (1) the decline of mobility function in PD, and (2) the effects of an engaging, cognitive game-based DT-walking program on mobility functions.

The first objective is to determine if the metabolic brain activity during single and DT treadmill walking is different in PD as compared to able-bodied age-matched controls. It is hypothesized that there will be significant changes in brain metabolic activity of several cortical and subcortical regions of the PD patients relative to able-bodied controls. This will be the case for both single and DT-walking conditions.

The second objective is to conduct a multi-centered, single-blind, randomized, two-arm, and parallel group-controlled trial and examine the effects of a 10-week DT treadmill training program: on (a) gate and cognitive function tested under single and DT conditions, (b) the pattern of metabolic brain activity quantified with single and DT-walking uptake periods, and (c) structural and functional changes (at rest) occurring prior to and after DT-walking training.

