For the neuroimaging data, Aim 1 will use PET data to compare levels of metabolic activity by region between; (a) single-walk only and DT-walk trials, and (b) PD and able-bodied age-matched controls. Aim 2 will use PET and MRI (RS-fMRI, pCASL, and DTI) data to investigate neural changes (whole-brain and ROIs) between pre- and post-intervention. See Table 1 for the ROIs to be used in the PET and RS-fMRI data for Aims 1 and 2. Paired sample *t*-tests will be conducted for these different neuroimaging modalities, with age and gender included as regressors of no interest. Additional correlational analyses are planned to investigate the relationship between changes in neural activity and behavioral metrics such as cognitive task performance and gait measures.

**TABLE 1 T1:** Regions of interest for the PET and fMRI ROI analyses.

**Amygdala, L**	**Dorsolateral PFC, L**	**Inferior Temporal, R**	**Mesial Temporal, L**	**Orbital frontal, R**	**Thalamus, R**
Amygdala, R	Dorsolateral PFC, R	Insula, L	Mesial Temporal, R	Putamen, L	Uncus, L
Anterior Cingulate, L	Frontal pole, L	Insula, R	Midbrain	Putamen, R	Uncus, R
Anterior Cingulate, R	Frontal pole, R	Lateral Temporal, L	Middle Temporal, L	Substantia nigra	Ventral Striatum, L
Subgenual cingulate (BA 25)	Hippocampus, L	Lateral Temporal, R	Middle Temporal, R	Superior Temporal, L	Ventral Striatum, R
Caudate, L	Hippocampus, R	Medial PFC, L	Occipital	Superior Temporal, R	Ventrolateral PFC, L
Caudate, R	Inferior Temporal, L	Medial PFC, R	Orbital frontal, L	Thalamus, L	Ventrolateral PFC, R

*L, left; R, right; PFC, prefrontal cortex.*

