##### FDG-PET Analysis

For FDG-PET data, an in-house whole-brain mask will be used as the explicit mask. PET images will be proportionally scaled to each image’s global values for statistical analysis. For both walk only and DT-walking conditions FDG-PET, ordinal trend/canonical variate analysis [OrT/CVA (Habeck et al., 2005)] will be applied to characterize the normal DT-walking-related brain metabolic pattern (NDWP), by comparing FDG-PET of single-walking vs. DT-walking in the healthy controls. First, the OrT transforms the preprocessed image data to increase the salience of ordinal trend effects, allowing the proceeding principal component analysis (PCA) to identify principal components with targeted expression (i.e., a consistent increase of pattern expression at the individual subject level), while also controlling for the salience of untargeted expression (Habeck et al., 2005). The principal components that result from the OrT can either be used individually, or can be linearly combined, allowing the expression of a given metabolic pattern to be quantified in each scan. Similarly, the PD-specific DT-walking-related brain metabolic pattern (PDWP) will be produced (i.e., DT-walking vs. single-walking in PD patients at pre-intervention). Additionally, we will examine if there is a different metabolic pattern, specific to the 10-week treatment-induced clinical benefits in PD by OrT/CVA (post- vs. pre-intervention during DT-walking). The topographical rating scale of the proposed FDG-PET patterns (i.e., NDWP, PDWP, and longitudinal pattern) will be computed in each FDG-PET image. Furthermore, behavioral scores (such as gait and cognitive performance) will be correlated with changes in metabolic patterns from pre- to post-intervention. The topography of the resulting spatial patterns will be compared using similarity test correcting for auto-correlation (Ko et al., 2014b).

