In regards to the pilot MRI data, we expect significant neural changes across modalities. Due to the importance of the dorsolateral PFC for both cognition and gait, we expect both PD groups to have reduced functional connectivity between this region and other basal structures compared to able-bodied controls using RS-fMRI data (Monchi et al., 2004; Nagano-Saito et al., 2014). We expect that following intervention, the XG group will have increased functional connectivity between these regions compared to the CG group, and that this functional connectivity will correlate with PD stage. Similarly, in the whole-brain RS-fMRI analysis, we hypothesize that pre-intervention, both PD groups will have altered functional connectivity within central executive, sensorimotor, visual, default mode, and cerebellar resting state networks compared to healthy controls (de Schipper et al., 2018; Wolters et al., 2019; Dong et al., 2020; Schneider et al., 2020), but that PD groups will not differ from each other. Post-intervention, we hypothesize that functional connectivity within these networks will differ between XG and CG PD groups. For the pilot pCASL data, we hypothesize that SVM-ISDA scores will not differ between PD groups at baseline, but will differ from able-bodied controls. Following intervention, we hypothesize that scores for both XG and CG groups will be reduced, with a larger effect observed for the XG group, indicating a larger treatment response. Although the DTI data are largely pilot data in nature, based on previous research indicating that reduced white matter integrity in forceps minor, corpus callosum, uncinate fasciculus, and cingulum is associated with reduced gait stability and may be associated with an increased risk of falling (Ghanavati et al., 2018; Snir et al., 2019), we hypothesize that the same relationship will hold in our sample. While it is thus far unclear whether structural changes in DTI can be observed in our population following 10-weeks of intervention, we expect that increased white matter integrity at post-intervention will be associated with improved gait stability and reduced number of falls at the 6-month follow-up.

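### The paired t-test named for the regional and whole-brain imaging contrasts cannot compare PD with controls or XG with CG, and no between-arm test is named for PET, pCASL or DTI

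*Protocol article*

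**What the plan says.** Objective 1 is to "determine if the metabolic brain activity during single and DT treadmill walking is different in PD as compared to able-bodied age-matched controls". Objective 2 is to "conduct a multi-centered, single-blind, randomized, two-arm, and parallel group-controlled trial and examine the effects of a 10-week DT treadmill training program"; its parts (b) and (c) are the metabolic pattern and the structural and resting functional measures.

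In Statistical Analyses, Aim 1 is to use PET to "compare levels of metabolic activity by region between; (a) single-walk only and DT-walk trials, and (b) PD and able-bodied age-matched controls". Aim 2 is to use PET and MRI "data to investigate neural changes (whole-brain and ROIs) between pre- and post-intervention". One test is then named for the modalities: "Paired sample *t*-tests will be conducted for these different neuroimaging modalities, with age and gender included as regressors of no interest". The preceding paragraph specifies a mixed ANOVA with a time-by-group interaction, but for behavioural outcomes only.

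Other sections add imaging analyses. FDG-PET Analysis derives one DT-walking pattern in controls and another in PD, scores the patterns in every image and compares their topographies with a similarity test. It also looks for a longitudinal pattern "specific to the 10-week treatment-induced clinical benefits in PD by OrT/CVA (post- vs. pre-intervention during DT-walking". RS-fMRI Analyses says global graph metrics will be compared between groups, naming neither the groups nor the test. pCASL Analysis uses change in classifier scores to assess treatment response, with no arm contrast.

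The hypotheses in Anticipated and Preliminary Results are about the arms. After the intervention, "we hypothesize that functional connectivity within these networks will differ between XG and CG PD groups", and pCASL scores are expected to fall in both arms, with a larger effect in XG.

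**The concern.** The named test does not fit one of the contrasts listed just before it, and it has no arm term for the randomised question. The text lists a PD-versus-control contrast and then gives a method that cannot carry it out, and it gives a time-by-group model for behaviour but not for imaging. That goes beyond detail an article may leave to an analysis plan.

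The inference about DT training is at stake. Both arms walk on a treadmill for 10 weeks, and all PD participants repeat the same DT PET protocol. Pre-post change will therefore include the effect of walking exercise, familiarity with the scan-day games and the course of the disease. The protocol itself predicts improvement in both arms. Only the difference between arms in change isolates the DT component.

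**Working it through.** **1. Matching each contrast to the named test**

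| Contrast | Where stated | Structure | Paired t-test valid? |
|---|---|---|---|
| Single vs DT walking | Aim 1(a) | Same person, two scans | Yes |
| PD vs controls | Aim 1(b), Objective 1 | 52 vs 15 different people | No |
| Pre vs post | Aim 2 as worded | Same person, two scans | Yes |
| XG vs CG | Objective 2(b)/(c), hypotheses | Two randomised groups | No |

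Matching on age does not create pairs at 52 versus 15, and no pairing is described. Age and gender are essentially constant across one person's scans, so their main effects cancel from a within-person difference. They matter mainly in the PD-versus-control comparison.

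**2. What the other imaging analyses cover**

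The similarity test asks whether two spatial patterns resemble each other. It does not test regional metabolism in PD against controls, or change in XG against CG. Pattern scores are computed, but no between-group test of them is named. The graph-metric comparison is confined to RS-fMRI. PET, pCASL and DTI are left without a named between-arm test.

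**3. Illustration: equal change in both arms**

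No figure in the plan bears directly on this point. The sample-size statement supplies the group size: 13 per group/site × 2 sites = 26 per arm. Assume both arms truly change by the same amount, dz, in SDs of the paired difference; these values are not in the documents. Test each arm with a two-sided paired t-test at 0.05, and let p be its power at n = 26. The arms are independent, so

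P(exactly one arm significant) = 2p(1 − p).

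| Assumed dz | p, one arm (n = 26) | P(exactly one significant) | Power, arms pooled (n = 52) |
|---|---|---|---|
| 0.3 | 0.313 | 2 × 0.313 × 0.687 = 0.43 | 0.56 |
| 0.5 | 0.688 | 2 × 0.688 × 0.312 = 0.43 | 0.94 |
| 0.8 | 0.975 | 2 × 0.975 × 0.025 = 0.05 | >0.99 |

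The true arm difference is zero in every row, so a valid between-arm test would be significant 5% of the time.

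**4. Precision of the comparisons that are needed**

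Assume 80% power, two-sided 0.05, one region and no multiplicity correction. The detectable d solves the noncentral-t power equation with noncentrality d × √(n1·n2/(n1 + n2)).

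- PD vs controls, 52 vs 15: √(780/67) = 3.41, detectable d = 0.83.
- Site-1 PD vs controls, 26 vs 15: √(390/41) = 3.08, detectable d = 0.93.
- XG vs CG on change, 26 vs 26: √13 = 3.61, detectable d = 0.79; with 24 vs 24 after dropout, 0.83.
- For comparison, paired pre-post: dz = 0.40 pooled (n = 52), 0.57 in one arm (n = 26).

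The 26-versus-15 figure matters because all controls are recruited at site 1. With an additive site term, site-2 patients have no controls to be compared with, so the group contrast rests on site-1 participants.

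**The case against.** The strongest reply is that this paragraph is not the whole imaging plan. The control and PD patterns with their similarity test partly address Objective 1, and the graph metrics are compared between groups. This stands in part. A reader might infer that the main imaging questions go wholly untested, and the documents do not support that. Neither analysis, however, replaces a regional PET group test or a between-arm PET test.

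Second, Aim 2 as worded is pre versus post, and a paired test fits it. That is correct. The arm question comes from Objective 2 and the stated hypotheses, so the defect is that the analysis does not reach the objective.

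Third, an article may leave arm terms to an unseen full document. That has some force for Objective 2 but none for Aim 1(b), where the contrast and an unsuitable test stand together.

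Fourth, the 43% figure depends on assumed effects, ignores dropout, and bites only if an arm difference is read from separate within-arm tests, which the article does not say will be done. This is fair; the figure illustrates a risk and does not predict a result.

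Fifth, the MRI measures are described as pilot. That also stands, so the weight of the point falls on PET.

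A reader might also infer false positives from testing all 42 listed regions at 0.05. The document does not support this: its 0.05 level appears in the paragraph on behavioural measures and SPSS, no imaging threshold is given, and correction is commonly left to the analysis plan.

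**Conclusion.** The point holds in this form. The only test named for the regional and whole-brain imaging contrasts is valid within a person, but not for PD versus controls or XG versus CG. The other described analyses fill the gap in part, and no between-arm test is named for PET, pCASL or DTI.

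The defect in Aim 1(b) follows from the text alone and needs no assumption. The size of the risk for Objective 2 depends on the shared change: misleading one-arm results in about 43% of trials at 0.3 or 0.5 SD and about 5% at 0.8 SD, with 26 per arm and separate two-sided tests at 0.05. A pooled pre-post test has no arm information at any effect size. The matter is most important for PET, where Objective 1 and Objective 2(b) depend on it, and less pressing for the pilot MRI measures.

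**What to change.** **Aim 1(b).** Specify an independent-groups model of PD versus controls for each uptake condition, plus the group-by-condition term, adjusted for age and sex. Because all controls are at site 1, make site-1 PD versus controls (26 versus 15) either the primary comparison or a stated sensitivity analysis. Report the loss of precision: detectable d of about 0.93, against 0.83 with all 52 patients.

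**Objective 2.** Compare post-minus-pre change, or baseline-adjusted post values, between XG and CG. Do this for regional PET values and OrT/CVA pattern scores from the DT scan (the only PET scan repeated after training), and likewise for the pilot MRI measures. Adjust for the stratification factors (Hoehn and Yahr stage, sex) and for site.

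**Keep** paired t-tests for Aim 1(a) and for describing change within each arm, and say that within-arm significance will not be read as evidence of an arm difference.

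**Cost.** The analysis text and design matrices are rewritten; scans, participants and software stay the same. The real price is precision: the arm contrast detects about 0.79 SD of change, where the pooled pre-post test detects 0.40. That is the cost of answering the randomised question.

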### Participants

52 patients with PD [26 from Winnipeg, MB, Canada (site 1) and 26 from Toronto, ON, Canada (site 2)], and 15 age-matched healthy, able-bodied control subjects (site 1) will be recruited in a 2-year time period. The criteria used for recruitment of the patients will include; (a) diagnosis of PD according to United Kingdom brain bank criteria (Hughes et al., 1992), (b) stage II-III of PD according to the Hoehn and Yahr scale (Bhidayasiri and Tarsy, 2012), (c) age 50–75 years, (d) adequate vision to see required images on a standard computer monitor, (e) able to score 26 or greater on the Montréal cognitive assessment scale [MoCA (Marinus et al., 2011)], (f) on stable medications for the past 3 months, and (g) able to walk overground for 2 min without an aid or cane. The exclusion criteria for participation will include the following: (a) diagnosis of any psychiatric comorbidity or history of any other neurological disease other than PD, (b) any other medical condition limiting participant ability to walk on the treadmill, and (c) neuroimaging contraindications (i.e., claustrophobia, severe dyskinesia, diabetes, non-compatible metal implants, etc.). Healthy able-bodied adults with the same inclusion/exclusion criteria listed above except for diagnosis of PD will be recruited.

All responders to calls for participation will undergo a screening assessment. Ethics approval has been obtained from the institutional Human Research Ethics Boards. All volunteer participants will be asked to read and sign the informed consent form. The Clinical trial has been registered at ClinicalTrials.gov, identifier: NCT04415775.

Successfully screened PD participants will be randomized to the experimental intervention (XG) or an active control arm (CG). A computerized block randomization procedure will be implemented by an independent statistician. Randomization will be stratified by stage of the disease (Hoehn and Yahr stage II and III). To ensure similar representation of men and women, randomization will also be stratified by sex. Randomization will be achieved by having participants choose an opaque sealed envelope, each containing a group assignment.

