**FIGURE 1 F1:**
[figure not shown]
Experimental timeline. Assessment days (ADay) indicate order of assessments. PET scans on ADay_3_ and ADay_4_ will be counterbalanced between a single-task treadmill walking only task and a DT treadmill walking and cognitive game condition. A final DT PET scan will be acquired following intervention (ADay_7_). MRI scans will be collected pre- (ADay_2_) and post-intervention (ADay_6_). Behavioral testing (Behav; including motor measures and neuropsychological testing) will occur on three occasions: prior to intervention (ADay_1_), following intervention (ADay_5_), and again after a 6-month follow-up. Fall-history and physical activity tracking will be acquired throughout, until 12-months post-intervention. Measures of gait will be acquired throughout the program, including during behavioral assessment days, at each training session, and on PET assessment days. The experimental (XG) and control arm (CG) groups will complete the entire timeline, while healthy controls (HC) will complete up until ADay_4_.

Participants in the CG group will complete 10 weeks of a “single-task” exercise program including videogames only (i.e., for 10 min while sitting) and walking-only on the treadmill—these tasks are conducted independently, one at a time. Participants in the XG will perform various cognitive computer games during the warm up period on the compliant surface and during all treadmill walking intervals. The computer games will be played using the head mounted IB-mouse as described above. Many inexpensive and easily accessible common and modern games exist which are visually rich, fun, and engaging. They include a variety of tasks that require; (i) visual search and tracking of multiple targets, (ii) speed accuracy requirements, (iii) presence of distracters, (iv) matching tasks, and (v) working memory. Note that the games that will be used during behavioral and PET assessments and those used in the XG exercise program are different.

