#### Image Acquisition

##### PET Data

All subjects will undergo two pre-intervention [^18^F] FDG-PET scans after fasting for at least 6 h before scanning. A head CT scan will be acquired for attenuation correction purposes. Static images (10 min) will be acquired starting 40 min after injection. During the FDG uptake period, participants will perform in different sessions, on different assessment days; (a) treadmill walking only (test session 1) and (b) DT treadmill walking (test session 2; see Figure 1). The order of the walk-only and DT-walking sessions will be counterbalanced. The single and DT treadmill walking will be done for 28 min each. This will involve seven 3-min walk intervals with 1-min rest periods (standing). Walking speed and duration will be carefully controlled, and repeated for each test session (i.e., single and DT conditions, pre- and post- intervention). Seven different standardized cognitive games will be selected for the seven DT-walking intervals. These will include; (a) five 3-min VC games with different difficulty levels (i.e., increasing game speed, adding distractors, and changing path of target motions), and (b) two 3-min VMT games, one played using horizontal head rotations and one with vertical head rotations. The PD patients will repeat the DT-walking PET imaging protocol after completion of the 10-week exercise program.

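### The paired test for single-task versus dual-task PET scans omits session order, so an order effect, if there is one, would be counted as error and could cost power for Aim 1(a)

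*Protocol article*

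**What the plan says.** Under PET Data, the two pre-intervention scans are made in separate sessions on separate assessment days: "The order of the walk-only and DT-walking sessions will be counterbalanced". The Figure 1 legend says the same of the third and fourth assessment days, which "will be counterbalanced between a single-task treadmill walking only task and a DT treadmill walking and cognitive game condition".

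Under Statistical Analyses, Aim 1 has two PET contrasts: "a) single-walk only and DT-walk trials, and (b) PD and able-bodied age-matched controls". Paired-sample t-tests "will be conducted for these different neuroimaging modalities, with age and gender included as regressors of no interest". No term for order, session or period is named there.

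Under FDG-PET Analysis, the normal DT-walking pattern is derived by OrT/CVA "by comparing FDG-PET of single-walking vs. DT-walking in the healthy controls", and the PD pattern is derived in the same way from the patients' pre-intervention scans. No order term is named there either.

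Under Participants, the article plans "52 patients with PD" and "15 age-matched healthy, able-bodied control subjects (site 1) will be recruited in a 2-year time period".

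**The concern.** The two scans form a two-period within-person comparison. Suppose the second session differs from the first, for instance because the participant has become used to 28 minutes of interval walking and to the scan procedure. The DT-minus-single difference then equals effect plus order in one sequence and effect minus order in the other. A plain paired t-test treats that systematic spread as noise.

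The article did choose nuisance regressors and wrote them down. Those it chose are constant within a person, so pairing has already removed their main effects. The factor that changes within the pair by design is missing. At stake is the precision of Aim 1(a), in controls and in patients. A larger error term makes a real regional difference easier to miss.

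**Working it through.** **The plan's own figure.** The article gives no power figure, order effect or SD for the single-versus-DT contrast. Its sample size rests on another quantity: f2 = 0.673/(1 - 0.673) = 2.058, which agrees with the stated 2.060 up to rounding. That calculation concerns how well a metabolic pattern explains clinical benefit, so it neither supports nor contradicts this point.

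**Inputs.** From the article: 52 patients, 15 controls, counterbalanced order, significance level 0.05 (stated in the paragraph on behavioural outcomes). Assumed: two-sided testing, one region at a time, a within-sequence SD of the paired difference of 1, sequence splits of 26/26 and 8/7, and an order effect pi between 0 and 1 in units of that SD.

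**Step 1: what each regressor can do.** In a stacked model for 15 people, subject plus condition has rank 16. Adding age and gender leaves it at 16, so their main effects adjust nothing. Adding period raises it to 17, so period can be estimated.

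**Step 2: variance.** With difference = d + pi in one sequence and d - pi in the other, plus noise of variance 1, the expected sample variance is 1 + pi² × [1 - ((n1 - n2)/n)²] × n/(n - 1). For 26/26:

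- pi = 0.25: 1 + 0.0625 × 52/51 = 1.064
- pi = 0.5: 1 + 0.25 × 52/51 = 1.255
- pi = 1.0: 1 + 52/51 = 2.020

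**Step 3: bias.** The plain mean is biased by pi × (n1 - n2)/n. This is zero for 26/26. For 8/7 it is pi/15, which is 0.033 SD at pi = 0.5 and 0.067 SD at pi = 1.0.

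**Step 4: power at n=52.** Simulation, 60,000 runs per setting, with d = 0.396 so that the plain test has 80% power when pi = 0:

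| pi | Plain paired t | With order term | Loss (points) | Type I error, plain |
|---|---|---|---|---|
| 0 | 80.1% | 80.1% | 0 | 4.9% |
| 0.1 | 79.8% | 80.0% | 0.2 | 5.0% |
| 0.25 | 78.3% | 80.2% | 1.9 | 4.4% |
| 0.5 | 72.6% | 79.9% | 7.3 | 2.9% |
| 0.75 | 63.3% | 79.7% | 16.4 | 1.4% |
| 1.0 | 50.1% | 79.7% | 29.6 | 0.6% |

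A separate run with d = 0.4 gave 74% v 81% at pi = 0.5 and 52% v 81% at pi = 1.0, losses of 7 and 29 points.

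**Step 5: the 15 controls (8/7, d = 0.8).** At pi = 0.5 the plain test has 78% power if the small imbalance pushes the estimate in the direction of the effect and 71% if it pushes the other way. The adjusted test has 81% in both cases. The plain test's type I error at pi = 0.5 is 3.1%, so the 8/7 bias does not make it anti-conservative.

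**Step 6: cost when there is no order effect.** Plain v adjusted power is 80.1% v 80.1% at n=52, 79.9% v 79.3% at n=15, and 80.0% v 79.1% at n=12.

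**The case against.** The strongest reply is that nothing here is invalid. A paired test on a counterbalanced design is sound, and a journal article may leave an image-model regressor to the full plan. Validity is conceded. The second part carries less weight, because the article does name the test and its nuisance regressors, so comment on that list is fair.

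The reply also holds that a large order effect is unlikely. Walking speed and duration are held constant across sessions, and each image is scaled to its own global value, which removes a purely global session shift. That stands. Only a region-specific order effect remains, and the article gives no evidence of its size. The losses of 16 points or more need an order effect of at least 0.75 SD.

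Four stronger readings are tempting, and the document does not support them:

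- *That power for Objective 1 is lost.* The loss is conditional. Objective 1 is also worded as whether "metabolic brain activity during single and DT treadmill walking is different in PD as compared to able-bodied age-matched controls", a between-group question. The point touches only contrast (a).
- *That the controls suffer most.* Step 5 shows that the answer turns on the sign of the order effect in the 8/7 split, which is unknown.
- *That age and gender are inert and should be dropped.* Only their main effects cancel. Regressed on the difference, they model variation of the condition effect by age or gender, which may be wanted.
- *That a period effect must be removed before OrT/CVA.* That method looks for a change in the same direction in every subject. A counterbalanced order effect has opposite signs in the two sequences, and no calculation shows that it distorts the patterns.

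**Conclusion.** The point holds as one of efficiency. The model named for Aim 1(a) leaves out the within-pair factor that the design itself introduces, and the covariates it includes do not stand in for it. The plain test stays valid and becomes conservative as the order effect grows.

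The size depends wholly on an order effect that the article does not give. At n=52 the loss is about 2 points or less up to 0.25 SD, about 7 points at 0.5 SD and about 29 to 30 points at 1.0 SD. These figures assume one region tested at two-sided 0.05 with about 80% power to start from. They show the pattern of loss and do not predict the power of the planned whole-brain and multi-region tests. The adjustment is worth making because it costs almost nothing if order does not matter and restores the power if it does.

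**What to change.** In the neuroimaging paragraph of Statistical Analyses, for the single-task versus DT PET contrast, add session order (first or second PET day) to the paired model. Equivalently, regress each person's DT-minus-single difference on sequence coded +1/-1 and test the intercept. With that coding the intercept weights the two sequences equally, which also removes the pi/15 bias in an 8/7 split. If age and gender are kept in this regression, mean-centre them so that the intercept remains the average condition effect, and state that they model age- or gender-by-condition variation. For the OrT/CVA patterns, at most report a sensitivity check by sequence.

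The change needs one regressor and one sentence. It needs no new data and no change in conduct, since each participant's order will be known. The downside is one degree of freedom: about 1 point of power or less if there is no order effect.
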